### Study Phase 2: Data Collection

Following software development, we received institutional review board (IRB) approval for phase 2. In this phase, we are conducting a mixed methods explanatory sequential designed study [14] for which we recruited 60 adults (aged ≥18 years) with T2DM. This is a 2-phase design where quantitative data are collected and followed by qualitative data collection. Patients were recruited from a primary care clinic associated with an academic medical center in the southeastern United States and through local advertisements. Eligible participants met the following inclusion criteria: (1) aged ≥18 years, (2) able to speak and read English, (3) diagnosed with T2DM, (4) told by their primary care provider to monitor their blood sugar, (5) own and use a smartphone, (6) capable of giving informed consent, and (7) able to travel for study enrollment. Participants were excluded if they had a preexisting severe medical condition(s) that would interfere with study participation (eg, renal failure, severe orthopedic conditions or joint replacement scheduled within six months, paralysis, or cancer). A proactive effort was made to enroll patients at various stages of diabetes mellitus, with treatment regimens including both oral and injectable medications were included. We purposefully targeted patients with a range of diabetes severity and included at least 25 patients with a hemoglobin A_1c_ (HbA_1c_)>7.5%. Patients were not required to have Wi-Fi or in-home internet; a smartphone with an internet connection was adequate. All other devices (eg, glucometer, cellular-enabled scale, and accelerometer) were provided to patients. Patients were excluded if they (1) had active dementia or psychiatric illness, (2) resided in a nursing home, or (3) were participating in another self-management study.

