#### Sample Size

Our goal is to obtain information critical to plan a larger trial and to understand how to use data from these trials in clinical practice. Accordingly, our sample size is based on our aims to determine feasibility and acceptability on using these devices and getting feedback from multiple stakeholders involved with their use, not on power to detect significant effects of self-monitoring on outcomes (eg, weight, HbA_1c_, and exercise). Our sample size of 60 patients is designed to provide a sufficient number of participants to obtain high retention rates, means, and variance estimates of end points that can be used to design and power the future trial. Our sample size of up to 20 clinician interviews is based upon estimates that we will likely reach data saturation within 12 or more interviews [15].

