### Data Analyses

All statistics will be calculated using SAS Version 9.3 (SAS Institute Inc.). Baseline demographic and clinical characteristics of enrolled participants are summarized by mean and SD for continuous variables and frequency and percentage for categorical variables. A significance level of 0.05 is considered as statistically significant for all tests.

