#### Patterns of Missing Data and Attrition

The primary analytical aim of this study is to estimate individuals’ performance of all the tasks involved in the daily monitoring of weight, exercise, and glucose and responding to the SMS text message surveys for medication adherence. A proxy for this estimate will be the percentages of the 180 days of data points from the Fitbit, the wireless scale, and the glucometer that were transferred. We will calculate the percentage of 180 days on which each type of data was transferred for each participant. Patient’s respondence to SMS text message surveys to medication adherence will be calculated by the number of surveys received out of 13 time points (baseline and every other week for 6 months). To examine if the performance of all tasks differ by important clinical groups, including age (<50 vs ≥50 years), HbA_1c_ group, (<7 vs ≥7, respectively), and race (white vs black or other non-white race), we will then test whether this percentage differed by different group variable using independent samples *t* tests.

To further explore the trend in performance of all tasks (using devices for daily monitoring), we will compute proportions of missing data for each person over 2-week time periods for the entire 6-month follow up time for weight, Fitbit, and blood glucose. We will construct empirical summary plot of biweekly missingness. This consisted of plots of mean percentage missing at each biweekly period over 13 biweekly periods. At each time point, bars representing 1 SE below and above the mean are also included. To examine if the trends differ by important clinical group variables, these plots will also be produced by different age group, HbA_1c_ group, and race. We will fit a generalized linear model with this proportion as the dependent variable. Predictors included age and HbA_1c_ group, and race, with each predictor tested in separate models. Time will also be included to assess change in biweekly missingness over time, as well as interactions between time and each predictor, to assess differences in change in biweekly missingness over time by age and HbA_1c_ group and race. We will also test the change in perceived usefulness and ease of use of the devices by conducting a paired *t* test on these measures between baseline and 6-month follow-up survey.

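### Age and HbA1c are cut into two groups and tested one factor at a time, which costs information in a sample of 60 and leaves the group contrasts unadjusted

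*Protocol article*

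**What the plan says.** All references are to the Protocol article.

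- **Groups.** Patterns of Missing Data and Attrition defines the comparison groups as "age (<50 vs ≥50 years), HbA_1c_ group, (<7 vs ≥7, respectively", plus race in two categories.
- **First analysis.** For the percentage of the 180 days with data transmitted, the plan will "test whether this percentage differed by different group variable using independent samples *t* tests".
- **Second analysis.** For the biweekly proportion missing it fits a generalized linear model with time and time interactions: "Predictors included age and HbA_1c_ group, and race, with each predictor tested in separate models". This could be read as leaving age continuous, but the accompanying plots are by age group, so the same split is the likelier reading. No model with the three factors together is described.
- **Recruitment.** Study Phase 2: Data Collection says the study "included at least 25 patients with a hemoglobin A_1c_ (HbA_1c_)>7.5" percent.
- **Sample size and testing.** Sample Size bases the 60 patients on feasibility, "not on power to detect significant effects of self-monitoring on outcomes". Data Analyses nevertheless sets a criterion for every test: "A significance level of 0.05 is considered as statistically significant for all tests".

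**The concern.** Cutting a continuous predictor in two treats everyone on one side of the cut as alike. If the outcome changes gradually with age or HbA1c, part of the available information is lost, and more is lost as the groups become less equal. With 60 participants there is little to spare.

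Testing each factor alone raises a second issue. Recruitment deliberately sought a range of diabetes severity and drew half the participants from the community through advertisements and flyers, so age, HbA1c and race may be associated in this sample. Separate models cannot show whether a difference by race or age partly reflects a difference in HbA1c.

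At stake is what the study can say about who stops transmitting data, which is useful for planning the larger trial named under Sample Size.

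**Working it through.** The article gives no power, effect size or information figure for these comparisons, so there is nothing of its own to reproduce.

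**Inputs from the article:** N = 60; cuts at age 50 and HbA1c 7; at least 25 participants above HbA1c 7.5%; significance level 0.05.

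**Assumptions:** two-sided tests, a normal predictor, a linear relation, and a range of split sizes and correlations, because the article gives none of these.

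**1. What recruitment guarantees.** Anyone above 7.5 is also at or above 7. If the same baseline value is used, the upper group therefore has at least 25/60 = 41.7% and the lower group at most 60 − 25 = 35. There is no minimum for the group below 7, and none on either side of age 50.

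**2. Information kept after the cut.** With a share p in one group, relative efficiency = φ(z_p)² / [p(1 − p)].

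- 50/50: 0.3989² / 0.25 = 0.637
- 20/80: 0.2800² / 0.16 = 0.490

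| Split | Information lost | Effective N of 60 |
|---|---|---|
| 50/50 | 36% | 38.2 |
| 42/58 | 37% | 37.6 |
| 30/70 | 42% | 34.5 |
| 25/75 | 46% | 32.3 |
| 20/80 | 51% | 29.4 |
| 10/90 | 66% | 20.5 |

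Sensitivity to the shape of the predictor: a uniform predictor cut at its median loses 25%; a strongly skewed one (lognormal, σ = 0.5) cut at its 25th percentile loses 68%.

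**3. Power for an assumed correlation r.** After the cut, r is multiplied by the square root of the efficiency. For r = 0.35 it becomes 0.35 × √0.637 = 0.279 at 50/50 and 0.35 × √0.490 = 0.245 at 20/80. Power comes from the noncentral t with 58 degrees of freedom and noncentrality √60 × r/√(1 − r²).

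| r | Continuous | 50/50 | 20/80 |
|---|---|---|---|
| 0.30 | 67% | 47% | 37% |
| 0.35 | 81% | 60% | 49% |
| 0.40 | 91% | 73% | 60% |

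Fisher's z approximation gives 79%, 58% and 47% for r = 0.35.

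**4. Smallest difference the t test detects with 80% power.** (1.960 + 0.842) × √(1/n₁ + 1/n₂), in SD units: 0.72 for 30/30, 0.73 for 25/35, 0.84 for 15/45 and 0.97 for 10/50.

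**5. Room for confounding.** Simulated with normal variables and median splits, where only HbA1c affects the outcome. The apparent age-group difference, as a share of the true HbA1c-group difference, is 0%, 10%, 30% and 50% for age–HbA1c correlations of 0, 0.1, 0.3 and 0.5. The article gives no such correlation.

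**The case against.** The strongest reply is that this is a feasibility study whose primary analysis estimates the percentage of days transmitted. The sample size is not power-based, and the Discussion concedes that the sample is too small for statistical conclusions. The group comparisons are secondary, and asking whether groups differ is a descriptive question that unadjusted contrasts answer directly. This limits the weight of the point. It does not remove it, because the plan still tests the groups and their time interactions at 0.05, and a small sample is a reason to use the data efficiently.

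The loss also rests on assumptions. A uniform predictor loses less, and if the true relation is a step near the cut, the loss need not arise. That stands, so the figures are conditional.

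A joint model has a cost of its own. HbA1c comes from the health record only where available, so participants without a value would drop out of the age and race estimates too. That also stands, and is why the joint model is proposed as support.

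Three stronger readings are tempting but not supported:

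- *That neither HbA1c group has a guaranteed size.* The recruitment minimum covers the group at or above 7; only the group below 7 has none.
- *That 7 in the analysis contradicts 7.5 in recruitment.* A recruitment minimum and an analysis group serve different purposes. Matching the cuts would not help, since a minimum above 7.5 sets none at or below it.
- *That the differences are confounded.* They are unadjusted and could be. The article reports no associations that would show it and claims no independent effect of any factor.

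**Conclusion.** The point holds as a low-cost improvement to secondary analyses. Splitting age at 50 and HbA1c at 7 loses about 36% of the information at an even split and about 51% at 20/80, given a normal predictor and a linear relation. The loss is larger for a smaller group and can be smaller or larger with other distributions. The actual loss cannot be computed, because the article does not give the split sizes. The power figures depend further on assumed correlations of 0.30 to 0.40.

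**What to change.** 1. In the transmission analysis, test age and HbA1c as continuous terms, for example per 10 years and per 1 percentage point, with a simple curvature check.
2. Use the same continuous terms, with their time interactions, in the biweekly missingness model.
3. Add one supporting model per outcome with age, HbA1c and race together, and report how many participants lack HbA1c and so drop out of it.
4. Keep the splits at age 50 and HbA1c 7 for plots and descriptive summaries, with the number in each group. The HbA1c cut need not match the recruitment threshold.

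No new data are needed. The costs are a linearity assumption to check, a few more parameters, and coefficients slightly less simple to present than two group means. Results reports patient data collection complete and analysis pending, so the change should be recorded as made at that stage.

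### The biweekly missingness model makes no provision for 13 correlated values per participant; fitted as named, its group tests are too liberal and its time and interaction tests are unreliable

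*Protocol article*

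**What the plan says.** All of this is in the Protocol article, Data Analyses, under Patterns of Missing Data and Attrition, unless another section is named.

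- **Outcome.** For weight, Fitbit and glucose, "we will compute proportions of missing data for each person over 2-week time periods for the entire 6-month follow up time".
- **Number of repeats.** The accompanying plots fix it: "This consisted of plots of mean percentage missing at each biweekly period over 13 biweekly periods".
- **Model.** "We will fit a generalized linear model with this proportion as the dependent variable".
- **Predictors.** Age group, HbA1c group and race, "with each predictor tested in separate models".
- **Time terms.** "Time will also be included to assess change in biweekly missingness over time, as well as interactions between time and each predictor".
- **Sample.** The Sample Size section gives 60 patients and says that the number was chosen for feasibility, "not on power to detect significant effects of self-monitoring on outcomes".
- **Level.** The opening paragraph of Data Analyses applies 0.05 to every test.

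The article mentions no random effect, repeated-measures structure, estimating equation or robust variance for this model.

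**The concern.** Age group, HbA1c group and race do not vary within a participant, so for those comparisons there are 60 independent units, not 780. A generalized linear model without a clustering device counts each row as new information.

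The study's own procedures make within-person correlation likely. Under Daily Monitoring, a participant who stays silent after two contacts is counted as withdrawn, so that person's later periods can be entirely missing. The article also names uncharged devices and lack of internet service as causes of non-transmission, and both can recur in the same person.

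At stake is whether the study reports that older or younger, better or worse controlled, or white and non-white participants disengage differently. This is the only model over time that the article describes, and the Sample Size section says the study is meant to inform a larger trial. A spurious group difference could be carried into that design.

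**Working it through.** **Inputs**

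| Input | Value | Source |
|---|---|---|
| Participants | 60 | Sample Size |
| Periods per participant, m | 13 (26 weeks / 2 = 13; 180 / 14 = 12.9) | Patterns of Missing Data and Attrition |
| Rows per device | 60 × 13 = 780 | arithmetic |
| Level | 0.05, two-sided assumed | Data Analyses |
| Intraclass correlation, ρ | 0.05 to 0.7 | assumption; the article gives none |

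The article states no power, effect size or standard error for this model, so there is no planned figure to reproduce.

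**Step 1. Group difference averaged over the 13 periods, exchangeable correlation.**
True variance / model variance = 1 + (m − 1)ρ = 1 + 12ρ.
Real type I error = 2 × [1 − Φ(1.96 / √(1 + 12ρ))].

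| ρ | 1 + 12ρ | True SE / reported SE | Real type I error |
|---|---|---|---|
| 0.05 | 1.6 | 1.26 | 12% |
| 0.1 | 2.2 | 1.48 | 19% |
| 0.3 | 4.6 | 2.14 | 36% |
| 0.5 | 7.0 | 2.65 | 46% |
| 0.7 | 9.4 | 3.07 | 52% |

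These figures are for the average group difference, that is, with time centred or group tested without the interaction. If group is instead read at time zero with periods coded 1 to 13, its variance under independence is proportional to 1/13 + 7²/182 = 0.346. The variance ratio is then (1 − ρ) + ρ/0.346, or 1.09 at ρ = 0.05 and 2.32 at ρ = 0.7. The real error is about 6% to 20%: smaller, still above 5%.

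**Step 2. Time and group-by-time, purely exchangeable correlation.**
True variance / model variance = 1 − ρ, so these tests are conservative. Real type I error is 4.4% at ρ = 0.05, 1.9% at ρ = 0.3 and 0.6% at ρ = 0.5.

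**Step 3. Simulation with no group difference.**
Setting: 500 runs per scenario, 60 people, 13 periods of 14 days, logistic random intercept with SD 1.2; where used, random slope SD 0.15 per period. These SDs are assumptions. Rejection rates at nominal 5%, Gaussian or overdispersed model first, plain binomial second:

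| Scenario | Group | Time | Interaction |
|---|---|---|---|
| Random intercept only (ICC 0.79) | 57% / 77% | 0% / about 3% | 0% / about 3% |
| Intercept and slope (ICC 0.66) | 55% / 78% | 19% / 54% | 18% / 53% |
| With 25% dropout added (ICC 0.60) | 47% / 76% | not reported | 20% / 56% |

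The group figures agree with Step 1: at ρ = 0.79 the factor is 1 + 12 × 0.79 = 10.5, which gives about 55%.

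**Step 4. Same mean model, standard errors clustered on participant.**
Random intercept only: group 4.0%, time 5.6%, interaction 5.2%. Intercept and slope: group 6.4%, time 7.6%, interaction 5.6%. With 500 runs the simulation error at 5% is √(0.05 × 0.95 / 500) = 1.0 percentage point. Clustering therefore removes most of the problem, and the 7.6% is a reason for a small-sample correction with 60 clusters.

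**The case against.** **The article does not say that rows are independent.** True. It names a model family and is silent on covariance, and a GEE is itself an extension of that family. A reader might infer that an analysis ignoring correlation was deliberately chosen; the text does not show that, and an unseen analysis plan may add clustering. What keeps the point alive is how much the article does fix: model class, outcome, predictors, separate fits, time and interactions. The same section says which t tests are for independent samples and which is paired. Only the model with 13 values per person lacks any such statement, and followed as written it has no means of handling the dependence.

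**The analysis is exploratory.** This stands. The article introduces it as a further exploration of trend. The primary percentages of 180 days, and the t tests by age, HbA1c and race, use one value per participant. The Discussion concedes that the sample does not support statistical conclusions. That caveat does not cure the model, because the tests remain planned at 0.05 and the fault makes the data look more informative than they are.

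**The sizes are assumed.** Also true. The article gives no intraclass correlation, slope variance or dropout rate, and no distribution for the model. The highest rates, 76% to 78% for group, need a plain binomial model that the article does not name.

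**Conclusion.** The point holds for an exploratory analysis and should be corrected before the model is run; it does not threaten the study's primary result.

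The group tests are too liberal at every correlation considered. Under exchangeable correlation the real error for the period-averaged difference is about 12% at ρ = 0.05 and 36% to 52% at ρ = 0.3 to 0.7, with smaller inflation if group is read at time zero.

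A reader might infer that every P value from this model will be too small. The documents do not support that. For time and interaction the direction depends on the pattern of non-use: conservative if participants differ only in level, anti-conservative if they differ in slope or drop out. Given the withdrawal rule the second pattern is the likelier, but the article has no figures to settle it. Nor do the documents support extending the fault to the 180-day percentages or their t tests.

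**What to change.** Replace the model sentence with wording such as: *The proportion of expected days missing in each two-week period will be modelled by GEE with a logit link, participant as the cluster, an exchangeable working correlation and small-sample-corrected robust standard errors.* In SAS this is GENMOD with a REPEATED statement or GLIMMIX with the EMPIRICAL option, choosing the route that supplies the correction. Three details should be settled with it:

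- **Denominator.** Use the days on which data were expected in each period, not a fixed 14. If 180 days are counted, 180 = 12 × 14 + 12, so the last period has 12 days. Table 1 has glucose measured as the physician prescribed, so its denominator should reflect the prescribed monitoring frequency; a day without a reading need not be a missing one.
- **One main model.** A GEE estimates a population-average effect and a mixed model a participant-specific one. Keep the GEE as the analysis and, if wanted, use a logistic mixed model with participant random intercept and slope as a sensitivity analysis.
- **Group term.** Centre time, or say at which period the group difference is read.

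The cost is a few lines of text and code, plus a record of prescribed glucose frequency if none is kept. No change to design or data from the devices is needed, and the Results section says that analysis was still pending. The downside is wider confidence intervals for the group effects.

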Those who failed to transmit data for a period of 7 days or longer were contacted over the phone by a research assistant to encourage reconnection with the study. If there was no response, the participant was contacted again via phone call or email 1 week later. Nonresponse at that time was considered elective withdrawal from the study. We attempted to contact any participants who withdrew to discuss their reasons for withdrawal. However, no more than 2 follow-up phone calls were made. We asked participants at baseline to please notify us of travel or other situations during which they were not able to transmit data. We made exceptions for participants who were on vacation or traveling. All mobile devices remained active until the end of the study to allow for reconnection at any point.

**Table 1 table1:** Mobile devices and data collection

Data	Instrument	Description	Data points
Exercise	Triaxial accelerometer and associated fitness app by Fitbit	Tracks data on the frequency and timing of steps	Daily: steps, minutes sedentary, minutes active, distance traveled
Weight	Cellular-enabled Scale by BodyTrace	Tracks weight	Daily weight
Glucose	Food and Drug Association–approved wireless glucometer by iHealth	Tracks blood glucose readings	As prescribed by primary care physician
Medication adherence	Self-report via short message service text message [23]	Medication adherence over the last week	Baseline, biweekly up to 6 months
Hemoglobin A_1c_	Electronic health record (EHR) laboratory results	Average level of blood sugar over the previous 3 months	Gathered from the EHR as available at baseline and 3 and 6 months post baseline

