#### Six Months Post Baseline

After 6 months, participants were sent a link via email to complete a follow-up survey on their experiences in the study; this was administered again using REDCap. Participants who completed the study and the final survey were able to keep the mobile devices.

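### The paired t test of perceived usefulness and ease of use describes only 6-month survey responders, who are likely to be the more engaged users, so the change is at risk of bias, probably in the favourable direction

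*Protocol article*

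**What the plan says.** Perceived usefulness and ease of use are measured at the baseline appointment. The protocol article (Patterns of Missing Data and Attrition) then fixes the analysis of these scores as a comparison, by paired t test, of the two surveys. The sentence opens: "We will also test the change in perceived usefulness and ease of use of the devices by conducting a".

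Three other statements decide who will have a second score:

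- Six Months Post Baseline: "After 6 months, participants were sent a link via email to complete a follow-up survey on their experiences in the study".
- Same section: "Participants who completed the study and the final survey were able to keep the mobile devices".
- Daily Monitoring: a gap in transmission of 7 days or more leads to a phone call. If there is no response, a second contact follows a week later. "Nonresponse at that time was considered elective withdrawal from the study". For those who leave, the plan says: "We attempted to contact any participants who withdrew to discuss their reasons for withdrawal". It does not mention asking them for the usefulness and ease-of-use scores again.

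Under Sample Size the article says that "our sample size is based on our aims to determine feasibility and acceptability on using these devices", and that the means and variances obtained are meant to help design and power a later trial.

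**The concern.** A paired t test leaves out anyone without a 6-month score. That does no harm if non-response is unrelated to change in perception. Here the design gives reason to expect a relation. The incentive to answer goes to people who completed the study, and people who disengage from the devices and from contact are classed as withdrawn. Disengagement from a device is plausibly linked to finding it less useful or harder to use.

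The primary measure treats such people differently. The percentage of 180 days with transmitted data is calculated for every participant, so someone who stops transmitting lowers it. The perception result omits the same person if the survey is not returned. Feasibility and acceptability could then describe different groups within one report. A mean change that holds for responders could be carried into the planning of the larger trial as if it held for all 60.

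**Working it through.** **No figure to reproduce.** The article gives no effect size, SD, withdrawal rate or expected survey response for this test. What follows is a sensitivity calculation on stated assumptions.

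**Inputs from the article.** 60 patients (Sample Size); significance level 0.05 (Data Analyses; two-sided is assumed here, since sidedness is not stated); paired t test, baseline to 6 months.

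**Assumptions.** The SD of the change score is 1, so results are in SD units. The share without a 6-month survey, m, is 10%, 20% or 30%. The gap g is the mean change in responders minus the mean change in non-responders, from 0 to 1 SD. The true mean change over all 60 is 0.

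**Bias.** The overall mean change is (1 − m) × responder mean + m × non-responder mean. Subtracting this from the responder mean gives

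bias = m × g.

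**Rejection rate.** The number of pairs is n = 60 × (1 − m). The test statistic follows a noncentral t distribution with n − 1 degrees of freedom and noncentrality m × g × √n. For example, at m = 0.20 and g = 1 the noncentrality is 0.20 × √48 = 1.39. At m = 0.30 and g = 1 it is 0.30 × √42 = 1.94.

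| Non-response | Pairs | g = 0: bias; rejection | g = 0.25 | g = 0.5 | g = 1.0 |
|---|---|---|---|---|---|
| 10% | 54 | 0; 5% | +0.025; 5.4% | +0.05; 6.5% | +0.10; 11.1% |
| 20% | 48 | 0; 5% | +0.05; 6.3% | +0.10; 10.4% | +0.20; 27.4% |
| 30% | 42 | 0; 5% | +0.075; 7.6% | +0.15; 15.8% | +0.30; 47.6% |

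The gap matters as much as the response rate. If non-responders changed more favourably than responders (g = −0.5), the bias is downward: −0.05, −0.10 and −0.15 SD at 10%, 20% and 30% non-response.

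**The same point seen from a result.** Suppose responders improve by 0.20 SD. The paired test then estimates +0.20 whatever happened to the others.

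- 20% missing, non-responders unchanged: 0.80 × 0.20 + 0.20 × 0 = +0.16.
- 20% missing, non-responders fall 0.5 SD: 0.16 − 0.20 × 0.5 = +0.06.
- 30% missing, non-responders unchanged: 0.70 × 0.20 + 0.30 × 0 = +0.14.
- 30% missing, non-responders fall 0.5 SD: 0.14 − 0.30 × 0.5 = −0.01.

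In the last case the apparent gain disappears over all 60.

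**The case against.** The strongest reply is that several separate things must coincide before there is any bias. Stopping transmission is not withdrawal: that needs non-response to two contacts, travel is exempt, and "All mobile devices remained active until the end of the study to allow for reconnection at any point". Data may also fail to arrive because a device was uncharged or there was no internet service, as the article itself says. Withdrawal is not survey non-response either, since nothing says that withdrawn participants were not sent the link. And the quantity tested is change, not level. People who disengage may have scored low at baseline and had less room to fall. All of this stands.

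A reader might therefore infer too much by saying that acceptability is overstated. The documents do not show that. They give neither a response rate nor perception scores by engagement. The favourable direction is likely, but it is an inference from the incentive and the withdrawal rule.

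It can also be said that this test is secondary, that 20 interviews will deliberately include inconsistent transmitters, that reasons for withdrawal are sought, and that the Discussion concedes the sample is too small for statistical conclusions. These points limit the importance of the problem but do not remove it. Interviews cannot correct a tested mean, and the listed limitations do not include responder selection.

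Finally, missing-data detail may sit in a full protocol or analysis plan that is not shown, and its absence from an article is no fault. The point rests instead on a method that the article does name, which by construction excludes non-responders.

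**Conclusion.** The concern holds as a risk of selection bias in a named secondary analysis. The paired t test estimates change among 6-month survey responders, who are likely to be the more engaged users. Any bias is probably towards favourable perceptions, but neither its presence nor its size can be established from the documents.

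Under the assumed 10% to 30% non-response and a gap of 0 to 1 SD, the bias is 0 to +0.30 SD. The two-sided rejection rate with no true mean change is 5% to about 48%. The upper end needs both 30% non-response and a full 1 SD gap. At a 0.5 SD gap the rate is 6.5% to 15.8%. The primary transmission percentages are unaffected, because they are calculated for every participant.

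**What to change.** Keep the paired t test and make four additions.

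1. Label the result as applying to 6-month survey responders, and report the number of pairs out of 60.
2. Compare responders with non-responders on baseline usefulness and ease-of-use scores and on the 180-day transmission percentages.
3. Add a sensitivity analysis covering all 60, by multiple imputation or a likelihood-based repeated-measures model, using baseline score, transmission percentages and withdrawal status.
4. Apply a delta adjustment to the missing 6-month scores over a range stated in advance, because imputation alone assumes the scores are missing at random. A shift of delta moves the mean over all 60 by m × delta. With 20% missing, a shift of −0.5 SD moves it by −0.10 SD.

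The Results section says that patient data collection is complete and analysis is pending, so these changes can still be made with data that the plan already collects. The cost is a few sentences and a little more analysis. The estimate for all 60 may be less favourable and less precise than the responders' result.
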